**Methods and analysis:**

We combine a cross-sectional observational study of child development and anthropometrics among approximately 4700 children aged 0–5 across 11 counties in Kenya with a cluster randomised controlled trial that measures the impact of improved daycare quality on these outcomes. We use International Development and Early Learning Assessment to measure child development and record child height and weight to measure height-for-age and weight-for-height z-scores. Primary analyses will (1) estimate associations between child development outcomes and nutritional status using multivariable regression models, adjusting for prespecified covariates; and (2) examine differences in outcomes between children attending daycares in communities exposed to quality improvements and children attending daycares in control communities. Subgroup analyses will examine heterogeneity by child sex and daycare participation.

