### Study objectives

To measure early child development in children 3–5 living in informal settlements in Kenya through the International Development and Early Learning Assessment (IDELA) and compare our results to existing measurements of child development outcomes found elsewhere.To assess the prevalence and severity of nutritional status deficiencies for children aged 0–5 living in informal settlements across Kenya through anthropometric measurements.To determine the correlates of both early child development and nutritional status, including whether paid caregiving arrangements are associated with children’s outcomes.To measure the causal impact of improvements in childcare quality on early child development and anthropometric measurements of nutritional status.

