### Data analysis

First, we will analyse and produce descriptive statistics of the key child development outcomes listed above. Second, we will compare these measurements for children in the treatment communities to those in control communities according to the larger study’s randomised design using multivariable regression. We will include controls for child age, sex and strata (county) fixed effects.

We will also examine these outcomes separately for the C-RCT baseline sample and daycare user sample. Because C-RCT baseline households were identified prior to randomisation and the intervention, we anticipate that differences in outcomes will reflect the causal intention-to-treat impact of improved childcare in the community. For the daycare user sample, we will capture the treatment-on-treated effect, but this could be biased if the quality improvement affected the selection of children into daycares.

We will restrict our child development analysis to children for whom we obtain IDELA data. Furthermore, we restrict our nutritional status analysis to children for whom we obtain valid anthropometric measurements. In the event of missing independent variables, we will code them as zero and include a missing variable flag.

Cross-sectional data gathered concurrently through caregiver and daycare firm surveys will produce a large dataset for measuring the relationship between early child development and nutritional status, as well as whether paid caregiving arrangements are associated with children’s health and development outcomes.

The final report of this study will follow the general CONSORT.

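### The zero-plus-flag rule for missing covariates is not confined to the trial regressions, and it leaves residual confounding in the primary association analysis

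*Protocol article*

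**What the plan says.** The abstract (Methods and analysis) lists two primary analyses. The first is to "estimate associations between child development outcomes and nutritional status using multivariable regression models, adjusting for prespecified covariates". The second is to "examine differences in outcomes between children attending daycares in communities exposed to quality improvements and children attending daycares in control communities". The third item under Study objectives repeats the observational aim: "To determine the correlates of both early child development and nutritional status, including whether paid caregiving arrangements are associated" with children's outcomes.

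The Data analysis section describes the treatment-control regression and names its adjustment set: "We will include controls for child age, sex and strata (county) fixed effects". It then deals with missing data in three sentences. Missing outcomes are handled by restriction: "We will restrict our child development analysis to children for whom we obtain IDELA data", and "we restrict our nutritional status analysis to children for whom we obtain valid anthropometric measurements". Missing regressors are handled by one general rule: "In the event of missing independent variables, we will code them as zero and include a missing variable flag". The next paragraph introduces the association analysis, which draws on the caregiver and daycare surveys. No other rule for missing covariates is stated for it.

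**The concern.** The two primary analyses use covariates for different purposes. In a randomised comparison, a covariate fixed before assignment is independent of arm. Handling its missing values crudely costs some precision but does not bias the treatment effect. In an association model, covariates are included because they are related to the exposure. If a child's confounder is replaced by a constant and a flag, the model cannot adjust that child's exposure for it. The pooled coefficient becomes a mixture of adjusted and unadjusted slopes.

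What is at stake is the estimated relation between nutritional status and development, and between paid care and outcomes. The error does not shrink as the sample grows, and it rises with the share of missing values. It also arises in the most benign case, where values are missing completely at random. The article has stated a method here, and that method does not suit one of its two primary analyses.

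**Working it through.** The article gives no missingness figure, so there is no stated number to reproduce. All effect sizes, correlations and missing shares below are assumptions. The only input taken from the document is the number of children with a development assessment, roughly 2700 (Background and rationale).

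**Formula.** Let the outcome be b_x·X + b_c·C + error, with X the exposure (for example the height-for-age z-score, HAZ), C a household confounder, both with unit variance, and correlation rho. Let C be missing completely at random in a share p, set to zero and flagged. Among children with C observed, the variation in X left after adjustment is 1 − rho². Among the others it is 1, and their slope is the unadjusted b_x + b_c·rho. Pooling gives

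estimate → b_x + w·b_c·rho, with w = p / [p + (1 − p)(1 − rho²)].

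**First scenario: b_x = 0.15, b_c = 0.35, rho = 0.4.** Here b_c·rho = 0.14 and 1 − rho² = 0.84.

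| Missing | w | Formula | Simulation (n = 4000, 300 repetitions) | Bias (simulation) |
|---|---|---|---|---|
| 5% | 0.05/0.848 = 0.059 | 0.158 | 0.158 | +5% |
| 10% | 0.10/0.856 = 0.117 | 0.166 | 0.167 | +11% |
| 20% | 0.20/0.872 = 0.229 | 0.182 | 0.183 | +22% |
| 30% | 0.30/0.888 = 0.338 | 0.197 | 0.197 | +31% |

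Complete-case analysis of the same data gave about 0.150.

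**Second scenario: b_x = 0.10, b_c = 0.30, n = 2700, 400 replicates per cell.** Entries are the mean estimate, with coverage of the 95% interval in brackets. Clustering was not simulated.

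| Missing | rho = 0.2 | rho = 0.3 | rho = 0.5 |
|---|---|---|---|
| 5% | 0.103 (96%) | 0.104 (95%) | 0.110 (91%) |
| 10% | 0.106 (94%) | 0.110 (94%) | 0.119 (86%) |
| 20% | 0.113 (91%) | 0.119 (83%) | 0.137 (57%) |
| 40% | 0.123 (74%) | 0.138 (46%) | 0.171 (5%) |

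The formula agrees: it gives 0.1381 at rho 0.3 and 0.1706 at rho 0.5 with 40% missing. When missingness of C depended on X, the bias had the same direction and similar or smaller size (0.138 and 0.164 in those two cells). Complete-case estimates lay between 0.0987 and 0.1015 in all cells with C missing, under both mechanisms.

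**Treatment contrast.** The same simulations included a randomised treatment with true effect 0.10. Its estimate stayed between 0.096 and 0.103 in every cell.

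**Exposure itself missing and flagged.** The HAZ slope was pulled slightly downward: 0.087 against 0.10 at rho 0.5 with 40% missing completely at random, and at least 0.096 for rho of 0.3 or less.

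**The case against.** **Scope.** The rule follows the paragraphs on the treatment-control comparison and precedes the one on associations, so it may have been written with the trial regressions in mind. A fuller analysis plan may say so. That possibility stands. But the sentence refers to independent variables without limit, and nothing else is offered for the associations. The controls named for the trial model are age, sex and county. County is known by design, and age is needed to establish eligibility. As worded, the rule would matter mainly where survey covariates enter, which is the association analysis.

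**Size.** The inputs are assumed, and the article describes high-frequency checks for unexpected missing values, so 20 to 30% missing may be pessimistic. This stands. In the first scenario at n = 2700, the standard error before clustering is about 0.9/√(2700 × 0.848) = 0.019, so the bias of 0.008 at 5% missing is under half a standard error. A reader might infer that missingness must be high because daycare families return only a consent form with a date of birth. The article does not say that household covariates are uncollected for them, and the appendix with the procedures is not shown.

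**Zero as a fill value.** A reader might think that coding a missing HAZ as zero, the WHO reference median, adds bias because this population lies well below it. It does not. Changing the fill value to any constant k adds k times the flag, which the flag's coefficient absorbs, so the HAZ slope is unchanged. The mild distortion shown above comes from the indicator method itself. The restriction to valid anthropometry may already remove such children, although the article does not say whether it applies when HAZ is a regressor for development scores.

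**The trial estimate.** Two opposite over-readings are tempting. One is that the treatment effect is biased too; for pre-randomisation covariates in the baseline sample it is not. The other is that the rule is safe in every treatment-control regression. Daycare users were recruited after randomisation, and the article concedes that treatment may have affected who enrolled, so independence of covariates and arm is not assured there.

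**Remedy.** Complete-case analysis was unbiased in the settings simulated, but it would not be if missingness depended on the outcome given the covariates. Multiple imputation was not simulated. Either can reasonably be primary.

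**Conclusion.** The point holds for the association analyses: as worded, the rule leaves residual confounding in primary analysis (1) and in the third objective, even under the mildest missingness. The direction follows the sign of b_c·rho. If better-off households have both better-nourished and more developed children, the nutrition-development slope is inflated.

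The size for this study is unknown. Across the assumed scenarios it runs from about 3 to 5% of the coefficient (5% missing, rho 0.2 to 0.3) to 23 to 71% (40% missing, rho 0.2 to 0.5). With little missing data and modest confounding, inference is hardly affected. For the baseline-sample treatment contrast, the rule is acceptable for covariates fixed before randomisation. For the daycare user sample that cannot be taken for granted. The rule should be corrected, but nothing here invalidates the trial comparison.

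**What to change.** Limit zero-plus-flag to pre-randomisation covariates, and fixed characteristics such as age and sex, in the treatment-control regressions.

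For the association analyses, and for any covariate measured after randomisation in the daycare user sample, name either multiple imputation of covariates or complete-case analysis as primary and report the other as sensitivity. The imputation model should include the outcome, county and community. State that the exposure of interest (HAZ, daycare use) is never flag-coded: children without it are excluded from that model, or it is imputed. Report the share missing for each covariate, so that readers can judge how much the choice matters.

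The cost is a sentence or two in the plan and a standard imputation run in Stata, the software already named. There is slightly more analysis work, and some loss of precision if complete-case analysis is chosen.

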#### Subsample analysis and heterogeneity

We will examine effects among our two different sample sources: the children recruited through our C-RCT household sample and those recruited from among children currently enrolled in the selected 220 daycares. We will also conduct subgroup analyses along the following dimensions:

Daycare enrolment status: whether using daycare or not; type of daycare used (home and centre vs school-based daycare) and quality of daycare used.Child sex.

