In this study, we build on an existing cluster randomised controlled trial (C-RCT) that has been underway in informal settlements in Kenya since 2024 and involves nearly 1000 daycare firms.^10^ We will collect and analyse data on child development for children aged 3–5 (roughly 2700 children) and child anthropometric measurements for children aged 0–5 (roughly 4700 children) in the same communities where these daycares operate. The intervention within the C-RCT focuses on improving the quality of paid daycare, including improvements in caregiving practices, infrastructure and the provision of nutritious food. The study sample includes (a) young children from households enrolled in the study before the intervention and (b) young children currently enrolled in centres located in treatment and control communities.

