## Methods: participants, interventions and outcomes

### Study background

The protocol described here builds on an ongoing C-RCT by (1) including a new sample of children enrolled in our study daycares and (2) collecting new data on anthropometric measurements and direct assessments of child development. The existing C-RCT measures the impact of a social franchising model designed to improve childcare quality on firms and families.^10^ We partnered with a Kenya-based social franchising organisation that supports and facilitates the improvement of existing daycare centres through training and continuous mentorship on various areas relevant to running a daycare, including high-quality caregiving practices, health and safety, and business management. The intervention also includes a facility improvement grant and is broad, with components that could improve child health and nutritional status both directly and indirectly. First, the organisation requires and supports improved sanitation practices (eg, installing wash stations, separating toileting from eating locations, etc). Second, it works to improve the physical infrastructure, such as providing rugs for floors. Third, it provides subsidised, fortified porridge for children. These intervention components may directly improve nutritional status and increase cognitive development of children through improved engagement and nutrition.

For the C-RCT, we randomly assigned 25 communities to receive the treatment and 26 to be in the control group, stratifying by county. The research team conducted this randomisation independently after the firm listing, firm baseline and household listing were complete, at which point it shared the assignment with the implementing partner. In treatment communities, the social franchising organisation offered its programme to all existing daycare firms, and it trained and enrolled those interested in its services. The organisation did not enter control communities, allowing us to compare impacts in areas with and without exposure to the franchising model. In this study,^10^ we measure the impact of this social franchising model on childcare quality, provider revenues and parental work outcomes in urban informal settlements across Kenya.

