### Firm recruitment

Within the 51 communities, we conducted a census of all paid daycares, and then a baseline survey with a subset in early 2024, reaching 978 providers. Our implementation partner then invited surveyed firms in treatment and control communities to attend a free half-day child development workshop. We denote the roughly 60% of baseline firms that attended this workshop as the ‘workshop sample’ (see Fitzpatrick *et al*^10^ for more details on their characteristics). In treatment communities, 82.5% of the workshop sample then opted to continue the partner’s programme, undergoing quality improvements and further training. Workshop-attending firms are comparable between treatment and control communities across the range of characteristics we consider, thus allowing us to use the ‘workshop sample’ to compare children in daycares that joined the social franchising organisation in treatment communities with children in daycares that would have likely joined the programme if the implementation partner had entered their community.

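### Daycare quality, which the programme is meant to change, is listed as a subgroup variable without being tied to values recorded before randomisation; daycare use and type share the problem only conditionally

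*Protocol article*

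**What the plan says.** Under Subsample analysis and heterogeneity, the article first promises effects by sample source. It then lists further subgroup dimensions: "Daycare enrolment status: whether using daycare or not", "type of daycare used (home and centre vs school-based daycare) and quality of daycare used", and child sex. No measurement time is given for any daycare variable. The Abstract repeats the plan: "Subgroup analyses will examine heterogeneity by child sex and daycare participation".

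Other sections describe what the programme does to daycares:

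- Background and rationale: "The intervention within the C-RCT focuses on improving the quality of paid daycare".
- Study background, on the parent trial: "we measure the impact of this social franchising model on childcare quality, provider revenues and parental work outcomes".
- Firm recruitment, on treatment communities: "82.5% of the workshop sample then opted to continue the partner’s programme, undergoing quality improvements and further training".

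On timing, the Data analysis section refers to "Cross-sectional data gathered concurrently through caregiver and daycare firm surveys", in a sentence about the association analyses. Child assessments are set for October 2025 and January 2026, in a trial running since 2024. For the daycare user sample only, the same section warns that the estimate is vulnerable: "this could be biased if the quality improvement affected the selection of children into daycares". No such warning accompanies the subgroup list.

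**The concern.** A subgroup analysis of a treatment effect keeps the protection of randomisation only if subgroup membership could not have been altered by treatment. Child sex meets that condition. Current daycare quality does not, because it lies on the causal path from the programme to the child.

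Two things go wrong when the arms are compared within a quality stratum. First, part or all of the mechanism is held fixed, so the contrast no longer measures what the programme achieves. Second, the groups stop being alike. A control daycare in the high stratum got there unaided, while a treatment daycare in that stratum may have been lifted into it. If whatever makes a daycare good unaided also relates to child outcomes, the control children in that stratum are the more advantaged. The same holds in the low stratum, where treatment daycares remain poor despite the programme.

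A working programme could then be reported as having no effect at any quality level. For daycare use, every child in the daycare user sample is a user, so non-users can come only from the C-RCT baseline sample. That is the sample the article relies on for its causal intention-to-treat estimate. If enrolment responds to the programme, splitting that sample by current use creates there the selection problem that the article acknowledges only for the other sample.

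**Working it through.** The article states no figure for these subgroups, so there is none to reproduce. The calculations below are illustrations. Every parameter is an assumption, except the 82.5% uptake and the roughly 60% workshop attendance, which are in Firm recruitment.

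**1. Split by current quality, full uptake**

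Let T be arm (0 or 1), U an unmeasured provider or household factor, and Q current quality, with independent standard normal noise terms e1 and e2:

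- Q = 0.8T + 0.6U + 0.8·e1, so Q has variance 0.36 + 0.64 = 1 within arm.
- Y = 0.2Q + 0.3U + 0.9·e2. The programme acts only through Q.
- The SD of Y within arm is √(0.04 + 0.09 + 2×0.2×0.3×0.6 + 0.81) = √1.012 = 1.006.

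Overall effect: 0.2 × 0.8 = 0.16, or about 0.16 SD.

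With equal arms the median of Q is 0.4. In the high half:

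- Control: share 1 - Φ(0.4) = 0.345; mean Q = φ(0.4)/0.345 = 1.069; mean U = 0.6 × 1.069 = 0.641.
- Treatment: share Φ(0.4) = 0.655; mean Q = 0.8 + φ(0.4)/0.655 = 1.362; mean U = 0.6 × 0.562 = 0.337.
- Contrast: 0.2 × (1.362 - 1.069) + 0.3 × (0.337 - 0.641) = 0.059 - 0.091 = -0.03.

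By symmetry the low half gives the same value. Simulation gives 0.161 overall and -0.032 in each half.

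**2. The same set-up with a weaker or absent confounder**

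- U coefficient 0.15: 0.059 - 0.15 × 0.304 = about 0.01 in each half.
- U coefficient 0: about 0.06 in each half, roughly one third of the total. Attenuation needs no confounding.

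**3. Partial uptake**

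Roughly 60% attended the workshop and 82.5% of attenders in treatment communities continued, so 0.60 × 0.825 = 0.495, or about half. With the quality shift reaching half of treated children and a U coefficient of 0.3, simulation gives about 0.08 SD overall and -0.01 to -0.02 SD within halves.

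**4. A second construction**

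Here uptake is 82.5%, the assumed quality shift is 0.5 or 1 SD, and high versus low is split at the control median.

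| How quality acts on the outcome | Confounder | Overall (SD) | Within strata (SD) |
|---|---|---|---|
| High vs low only | no | 0.08 to 0.14 | 0.00 to 0.01 |
| High vs low only | yes | 0.07 to 0.13 | -0.05 to -0.03 |
| Continuously | no | 0.10 to 0.20 | 0.03 to 0.10 |
| Continuously | yes | 0.09 to 0.19 | -0.01 to 0.05 |

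**5. Split by current use**

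Assume a true effect of zero, 40% enrolment in control, a correlation of 0.3 in absolute value between U and the propensity to enrol, and an outcome loading of 0.5 on U. Among users the mean of U is ±0.3 × φ(z)/p at enrolment p. The size of the bias is therefore 0.5 × 0.3 × the change in φ(z)/p:

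- No change in enrolment: 0.
- 40% to 45%: 0.15 × (0.966 - 0.880) = 0.013 SD.
- 40% to 50%: 0.15 × (0.966 - 0.798) = 0.025 SD.
- 40% to 55%: 0.15 × (0.966 - 0.720) = 0.037 SD.

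The sign depends on who newly enrols. Simulated values for users and non-users lie in the same range, about 0.01 to 0.04 SD. Daycare type would follow the same logic, but the article gives nothing from which to size it.

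**The case against.** Several counter-arguments have weight.

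- **Timing is inferred.** The subgroup list gives no measurement time, and the sentence about concurrently gathered data concerns the association analyses. The fuller plan, which is not shown, may specify baseline values. This stands. But nothing in the article points to baseline, and the wording refers to the daycare a child uses. If baseline is meant, one phrase settles it.
- **Not every split need be an arm contrast.** The article also has descriptive and associational aims, for which current use, type and quality are suitable variables. That is true, and those analyses are not criticised here. However, the list follows a sentence about effects, under a heading on heterogeneity, beside child sex.
- **Only quality is a stated target.** A reader might infer that the programme changes use and type as well, so that all three subgroup effects are certainly biased. The documents do not support this. Changed selection into daycares is raised only as a possibility and only for the daycare user sample, and no section says that daycare type changes.
- **The sizes rest on chosen parameters.** This stands. A complete disappearance of the effect is one outcome among several; with quality acting continuously and no confounder, 0.03 to 0.10 SD remains.
- **These are secondary analyses.** This also stands, and it limits the severity.

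**Conclusion.** The point holds in full for daycare quality and conditionally for use and type. If quality is measured after randomisation, arm contrasts within quality strata condition on a mediator and cannot be read as effect heterogeneity. Under the assumed parameters an overall 0.16 SD falls to about 0.06 SD within strata without a confounder and to about -0.03 SD with one. The exact size is not known, but contrasts within strata were smaller than the overall effect in every scenario tried. For use and type there is no bias if the programme leaves them unchanged. For use, the bias is small (about 0.01 to 0.04 SD) for enrolment shifts of 5 to 15 points.

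A reader might go further and conclude that the trial's main result is compromised. It is not: the overall intention-to-treat comparison and the child-sex subgroups are unaffected. This is a should-fix matter, resting on the inference that the daycare variables describe status at assessment.

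**What to change.** State when each daycare subgroup variable is measured. Then:

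1. For heterogeneity of treatment effects, take daycare type and quality from the early-2024 firm baseline, where recorded. Take the child's daycare use from household data collected before randomisation, where recorded. Test treatment-by-subgroup interactions on these.
2. Report current use, type and quality as outcomes compared by arm. Alternatively, keep the splits by current status but label them descriptive or mediation analyses, and not effect heterogeneity.
3. Extend the existing caution about selection into daycares to any split by current use or type.

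The cost is mainly wording, provided the data exist. The article says that the firm listing, firm baseline and household listing preceded randomisation. It does not say that each child's daycare use was recorded then; if it was not, the split by use should be labelled descriptive. The other downside is precision of meaning: the article reports high turnover in daycare enrolment, so baseline status will describe current exposure less well. The change should be settled before outcomes are compared by arm.
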